**Fig. 2 Fig2:**
[figure not shown]
Standard Protocol Items: Recommendations for Interventional Trials (SPIRIT) Figure. *IPAQ* International Physical Activity Questionnaire, *SF-36* Short Form 36, *WOMAC* Western Ontario and McMaster Universities Arthritis Index, *5STS* Five-Times-Sit-To-Stand Test, *TUG* Timed Up and Go Test, *6MWT* 6-minute walk test

### Primary and secondary outcomes

The primary outcome is the difference in enhancement of the 6MWD between intervention and control group in meters after 3 months. The 6MWT is an objective assessment [20] that has been found to detect functional improvement after total hip and knee replacement [29–32].

To provide a comprehensive comparison between the two groups, a battery of questionnaires, functional and measures of function will also be investigated:

### Differences in the improvement of the:

Return to work statusIPAQ score (points)SF-36 Physical and Mental Component Summaries (points)WOMAC score (points)Postural control (double-footed and one-leg stance): the overall displacement of the center of pressure (mm) for the 30 s (first 10 s) time intervalGait analysis: gait velocity (m/s); step length/width (cm); maximal, minimal and mean ankle, knee, hip joint angles (°)Stair Ascend Test (s)Five-Times-Chair-Rise Test (s)Timed Up and Go Test (s), andTraining adherence after the intervention time of 3 months

### Statistics and power calculation

Data will be evaluated descriptively (mean, standard deviation, 95% confidence interval and median for metric variables, frequency and percentiles for categorical variables) for all variables as available case analysis. Inferential statistics will be performed using an intention-to-treat approach including all randomized patients and with multiply imputed data sets for evaluation of the effectiveness of the intervention, as well as a per-protocol approach in patients with complete data sets and without protocol violations for evaluation of the efficacy of the intervention. Baseline-adjusted analysis of covariance (ANCOVA) models (intention-to-treat) will be used to test the primary endpoint for group differences at a level of 5% (two-sided). All continuous secondary endpoints will be analog-tested without adjustment for multiplicity. The rates of return to work status will be compared with the Likelihood-Ratio-Chi^2^-Test. Model assumptions will be checked by testing site × group interactions as extensions of the analysis of covariance (ANCOVA) models.

According to Boardman et al. [30], an improvement of 65–70 m in 6MWD is to be expected by knee or hip replacement followed by standard orthopedic rehabilitation. The study was powered to be able to demonstrate a further improvement of 65 m by telerehabilitation as compared to an improvement of not more than 13 m (20%) in the control group. Assuming an intraclass correlation of 0.3 for the primary outcome and a standard deviation of 84 m [30, 33], 42 patients per group will be needed to reach a power of 80% for the primary analysis. Presuming a 20–25% loss to follow-up, 55 patients per group need to be included in the study to reach the same power in the per-protocol analysis, resulting in a recruitment and randomization of 110 patients in total.

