## Methods/design

### Study design

In this multicenter, no-blinded, parallel-group randomized controlled trial, patients after hip or knee replacement with a subsequent orthopedic rehabilitation are enrolled in the three participating inpatient rehabilitation centers in Germany. In this study, blinding was not possible due to the nature of the intervention. Assessments are carried out by research associates of University Outpatient Clinic of the University of Potsdam (study site), who are also responsible for giving out the telerehabilitation system to the patients of the intervention group.

The patients are either randomized into the intervention or the control group, using a block randomization with a ratio of 1:1, stratified by the inpatient rehabilitation center. The random code was prepared by the statistical institute in advance and is centrally managed by the study site. The patients are investigated and assessed at the study site within 7 days after their inpatient rehabilitation (Fig. 1).

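### Randomisation is stratified by rehabilitation center, but the stated ANCOVA models have no center main effect: slightly conservative, and free to correct

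*Protocol article*

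**What the plan says.** The Study design section says that patients "are enrolled in the three participating inpatient rehabilitation centers in Germany" and are allocated "using a block randomization with a ratio of 1:1, stratified by the inpatient rehabilitation center".

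Statistics and power calculation gives the primary analysis: "Baseline-adjusted analysis of covariance (ANCOVA) models (intention-to-treat) will be used to test the primary endpoint for group differences at a level of 5" percent, two-sided. The continuous secondary endpoints are to be tested in the same way, and the abstract gives the same baseline-adjusted model for primary and secondary endpoints.

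Center has one role in the analysis: "Model assumptions will be checked by testing site × group interactions as extensions of the analysis of covariance (ANCOVA) models". The article uses the term study site for the single university clinic where all assessments take place, so site in this sentence presumably means the rehabilitation center. No section names center as a main-effect covariate.

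**The concern.** Blocking within center makes the two arms nearly equal in size in each center, so differences between centers largely cancel from the treatment comparison. A model with group and baseline alone does not know this. Any center variation that baseline does not explain is counted as residual noise, and the reported standard error is larger than the true sampling variation of the estimate.

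Some center effect is conceivable. Each center delivers its own inpatient stay, and its physiotherapist writes and monitors the training plan in the intervention arm. What is at stake is a little precision and power, given up although the design has already paid for it.

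**Working it through.** **1. The plan's own sample size.** Inputs from Statistics and power calculation: "a further improvement of 65 m by telerehabilitation as compared to an improvement of not more than 13 m (20%) in the control group", hence a difference of 65 − 13 = 52 m; SD 84 m; two-sided 5%; power 80%.

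- Normal approximation: n = 2 × (1.960 + 0.842)² × 84² / 52² ≈ 41 per group.
- Noncentral t: n = 42 per group, power 80.05%.

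The stated 42 is reproduced as a plain two-sample t-test. It uses neither a center term nor the intraclass correlation of 0.3 quoted beside it. Variants that use the 0.3 do not give 42: SD × √(1 − 0.3²) gives 38 (39 with t), and SD × √(2 × (1 − 0.3)) gives 58 (59 with t). The planned size therefore does not depend on whether center is in the model.

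**2. Analytic size of the effect.** Let R² be the share of residual 6-minute walk distance variance due to center. The article does not give it, so this is an assumption. With balance forced within center, true SE = √(1 − R²) × SE from the model without center. The model SE is therefore too large by a factor 1/√(1 − R²), and the actual two-sided level is 2 × [1 − Φ(1.96/√(1 − R²))].

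- R² = 0.02: factor 1.010, SE 1.0% too large, level about 0.048.
- R² = 0.05: factor 1.026, SE 2.6% too large, level about 0.044.
- R² = 0.10: factor 1.054, SE 5.4% too large, level about 0.039.

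**3. Simulation.** Assumptions: three equal centers, blocks of 4 within center, baseline–outcome correlation 0.3, total SD 84 m, true difference 0 or 52 m, 6,000 runs per cell. Here the share is of total outcome variance, and the center effect is independent of baseline. Results with 84 analysed (42 per group), ANCOVA without center versus with center:

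| Center share | Mean SE (m) | Type I error | Power |
|---|---|---|---|
| 0% | 17.5 vs 17.5 | 4.8% vs 4.7% | 83.6% vs 83.5% |
| 2% | 17.6 vs 17.4 | 4.8% vs 5.1% | 83.1% vs 83.5% |
| 5% | 17.5 vs 17.0 | 4.2% vs 4.7% | 83.8% vs 85.2% |
| 10% | 17.6 vs 16.5 | 3.8% vs 5.1% | 84.8% vs 87.6% |
| 30% (extreme) | 17.6 vs 14.4 | 1.8% vs 5.0% | 87.2% vs 94.5% |

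The Monte Carlo error of a 5% rejection rate is √(0.05 × 0.95 / 6000) ≈ 0.3 percentage points, so 4.7% and 5.1% are both compatible with 5%. Power without center rises slightly with the share because total SD is held at 84 m, which leaves less variation within centers.

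The actual spread of the estimate under no treatment effect confirms the direction. At a 10% share the model without center reports a mean SE of 17.6 m, while its estimates have an SD of 16.7 m. At 5% the figures are 17.5 and 17.0 m.

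With 110 analysed, the power gap is smaller: 92.3% vs 93.2% at a 5% share and 92.9% vs 94.2% at 10%.

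**The case against.** **The article does not say that baseline is the only covariate.** It is a condensed account, and a separate analysis plan could list center. This stands as a limit on certainty: the absence of center is inferred. But the article does fix the test, the adjustment and the level, and it brings site in only as an extension of the model. The natural reading is that the base model has no site term. If an analysis plan includes center, the published description needs one added phrase.

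**The center share may be very small.** Baseline is measured after the inpatient stay and so already carries part of any difference between centers. All assessments are made at one university clinic under a standard operating procedure. This stands, and at a 0–2% share adjustment gains almost nothing. It also costs almost nothing: with no center effect, power is 83.6% without the term and 83.5% with it.

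**Stronger readings that the document does not support:**

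- *The test is invalid.* A reader might infer this from standard errors that ignore the stratification. The error runs the other way, and a positive result would stand.
- *The site × group test is mislabelled as an assumption check.* A main-effects ANCOVA assumes one treatment effect across centers, and this test examines that assumption. It is legitimate, but it does not replace a center main effect.
- *The centers run different programs.* The section on the inpatient program describes one set of main components for all three.
- *The intraclass correlation of 0.3 is the center share.* The text does not say what it refers to, and the sample size is reproduced without it.
- *The return-to-work test is wrong* ("The rates of return to work status will be compared with the" likelihood-ratio chi-square test), *or a baseline × group check is missing.* The first is an acceptable unadjusted test, and an adjusted model would be a preference. Model diagnostics are detail that an article may leave to the analysis plan.

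**Conclusion.** The point holds as a modest mismatch between design and analysis. The allocation is stratified by center, and the stated primary and continuous secondary models do not carry center as a main effect. The consequence is conservative only: the standard error is about 2.6–5.4% too large and the nominal 5% test runs at roughly 4.4–3.9% if center explains 5–10% of residual variance. Power loss with 84 analysed is about 1 point at a 5% share and about 3 at 10%, and is negligible at 0–2%. These figures rest on an assumed center share and, in the simulation, on equal centers, blocks of 4 and a baseline correlation of 0.3. The direction does not depend on the share chosen. The planned sample size is unaffected.

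**What to change.** State the primary ANCOVA, and each continuous secondary ANCOVA, as:

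3-month value = group + baseline value + rehabilitation center (three-level fixed effect).

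Keep the site × group test as the check of a common treatment effect across centers, and say that site there means the rehabilitation center. If an analysis plan already includes center, bring the published wording into line with it.

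The cost is 2 degrees of freedom and a wording change, to be recorded before the outcome data are analysed. Center is known for every patient because it was used for randomisation, so no new data are needed. The sample size stays at 110.

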## Discussion

The medium- and long-term sustainability of maintaining the therapeutic success of rehabilitation programs remains a major challenge. Treatment options after rehabilitation are often far away and difficult to access. Therefore, telerehabilitation could have the potential to increase the access to therapy in structurally weak areas, where appropriate healthcare structures and offers are missing, as it promises to increase patient access, improve quality and reduce costs in healthcare [13]. For patients, especially after orthopedic surgery, telerehabilitation seems to be a promising offer for the recovery of motor function [17, 34] which might be useful for longer distances to work and for coping with challenges of everyday life. Therefore, we concentrate on functional outcomes, such as the 6MWT, as the primary outcome to prove the effectiveness of our telerehabilitation system. The 6MWT is a strong predictor for mobility and functional recovery after hip or knee replacement [30, 31]. To achieve a complex representation of both functional and emotional status, which need to be considered in a rehabilitation process, further investigation of the secondary endpoints to show differences in mobility, strength, postural control as well as health-related quality of life and pain seems appropriate.

It is well known that the compliance of patients performing home-based exercises needs to be improved and the flexible use of telerehabilitation could increase the adherence [35]. The reasons for the non-compliance of the patients are suggested to be the absence of positive feedback as well as a degree of experienced helplessness [36]. Solutions for this problem could be setting goals, being monitored and receiving feedback [37] by using telerehabilitation systems. In our study, we expect a strong adherence in the intervention group due to the close monitoring of the supervising physiotherapist in the rehabilitation center, who is familiar with the patients because of their previous inpatient stay. With scheduled, weekly video-conferences and the steady possibility to communicate via text or voice messages, the patients might greatly benefit regarding the motivational component of being physically active. We are able to examine the adherence of the patients with the training diary, which every patient in both groups has to fill out weekly. It is also conceivable that the improvements in the control group result from more elaborate program and treatment frequency of the voluntary usual aftercare.

Due to the fact that blinding of the research associates is not possible, we cannot rule out that the patients could possibly be influenced during the measurements. Furthermore, we need to exclude patients without expected functional safety in walking with full load at the end of the rehabilitation, which might be a selection bias. This patient selection compromises the generalizability of the results, but presumably does not bias the comparison between random groups.

In conclusion, we expect the intervention group to benefit from the interactive, home-based, exercise training concerning the outcome. If successful, this approach could be used to enhance the access to aftercare programs, especially in structurally weak areas.

## Trial status

Recruitment has begun in August 2016. Up to now (05/2017), 87 patients are included.

## Abbreviations

5STS: Five-Times-Sit-To-Stand Test
6MWD: 6-minute walk distance
6MWT: 6-minute walk test
ANCOVA: Analysis of covariance
HDMI: High Definition Multimedia Interface
IPAQ: International Physical Activity Questionnaire
OECD: Organization for Economic Co-operation and Development
SF-36: Short Form 36
SPIRIT: Standard Protocol Items, Recommendations for Interventional Trials
TUG: Timed Up and Go Test
WOMAC: Western Ontario and McMaster Universities Arthritis Index
